## Abstract

**Background:**

Anti-NMDA receptor encephalitis (NMDARE) is the most common autoimmune encephalitis, involving an immune response against NMDA receptors on neurons. Despite standard immunotherapy, approximately 30% of critically ill patients require long-term intensive care. Current management strategies are mainly based on retrospective studies and expert opinions, with limited high-quality evidence. This study aims to evaluate the efficacy and safety of B-cell depleting agents followed by daratumumab as a second-line treatment for severe autoimmune encephalitis (AE) with NMDARE as the primary target population.

**Objective:**

To describe the study protocol for the RADIA study.

**Study design:**

This multicenter, open-label, randomized controlled trial is conducted across 58 tertiary hospitals in China. Eligible participants are patients with severe AE especially NMDARE (mRS ≥ 3 points and neuropsychiatric manifestations inadequate to symptomatic treatment) post first-line immunotherapy. A total of 200 patients will be randomized at a 2:2:1 ratio into three groups. 80 patients will receive B-cell depleting agent (anti-CD20 mAb ofatumumab) followed by anti-CD38 mAb daratumumab, 80 patients will receive B-cell depleting agent ofatumumab alone, and 40 receive repeated IVIG or plasmapheresis.

**Main outcome measures:**

The primary endpoint is the proportion of patients with an mRS score ≤ 2, assessed at 16 weeks after treatment initiation. The secondary outcomes include scores on the Clinical Assessment Scale for Autoimmune Encephalitis (CASE), neurocognitive function, antibody status, ICU stay, and hospitalization duration up to 48 weeks. Adverse events will be monitored continuously.

**Conclusion:**

This trial aims to provide robust data on the efficacy of B cell depleting agents followed by daratumumab in patients with severe AE, with a primary focus on the NMDARE subgroup. This combined regimen may provide a new treatment option for NMDARE.

**Clinical trial registration:**

https://clinicaltrials.gov/study/NCT06867991, identifier (NCT06867991).

## Introduction

1

Autoimmune encephalitis (AE) is a spectrum of inflammatory disorders in the central nervous system, usually driven by aberrant immune responses targeting neural antigens including surface antigens and intracellular antigens (1). The underlying immunopathology in individuals with neural surface autoantiboides is believed to be antibody mediated, irrespective of the presence of neoplasms. Though AE is a rare heterogenous disease, it can affect patients of all ages, both in children and young adults (2). Anti-N-methyl-D-aspartate receptor encephalitis (NMDARE) is the most common AE, followed by leucine-rich glioma-inactivated 1 (LGI1), gamma-aminobutyric acid type B receptor (GABABR), contactin-associated protein-like 2 (CASPR2) and other encephalitis (3). AE usually presents with mental and behavioral changes, seizures, movement disorders, and autonomic dysfunction. Severe cases may have impaired consciousness, status epilepticus, status dystonia, autonomic instability, and central hypoventilation requiring mechanical ventilation (4). Current treatment regimens often adopt a stepwise approach. First-line immunotherapies include intravenous methylprednisolone (IVMP), intravenous immunoglobulin (IVIG), and plasma exchange (PE) or immunoadsorption. For patients who show inadequate responses to initial treatments, second-line therapies are used, including B-cell depleting therapy (BCDT) or cyclophosphamide (5, 6). Rituximab is the most frequently used anti-CD20 monoclonal antibody (mAb) in AE.

Real-world evidence from the GENERATE registry has demonstrated that rituximab, the most frequently used anti-CD20 monoclonal antibody in AE, is associated with improved functional outcomes in NMDAR, LGI1, and CASPR2 encephalitis and a reduced relapse rate, although limited benefit is observed in long-standing GAD65 disease (7). Recent studies showed that another mAb, ofatumumab, which was approved in multiple sclerosis, may also have a beneficial effect on AE. More recently, the prospective OFF-AE cohort study reported that ofatumumab, a second-generation anti-CD20 antibody, led to further functional improvement in 93.1% of NMDAR encephalitis patients, with a particularly favorable effect in those who failed first-line immunotherapy (87.9% vs. 64.7% achieving mRS ≤ 2) and no serious adverse events (8). However, a recent real-world prospective cohort study involving severe anti-NMDAR encephalitis found that only 63.9% of ofatumumab-treated and 55.6% of rituximab-treated patients achieved a good outcome [modified Rankin Scale (mRS) ≤ 2] at 3 months, although BCDT significantly improved outcomes compared to conventional first-line immunotherapy alone (9). Another report showed that approximately 30% of critically ill patients do not respond to these existing treatments and require long-term intensive care support (10). Therefore, there are still urgent unmet needs for severe patients with AE to achieve a good outcome.

Plasma cells reside within the central nervous system and its borders, where they contribute to both protective humoral immunity and pathological inflammation (11). Pathological studies found a significant infiltration of antibody-secreting cells (CD38^+^ CD138^+^) into the brain tissue of AE patients (12, 13). These cells are found around blood vessels, within interstitial spaces, and in Virchow-Robin spaces, where they continue to secrete autoantibodies, thus explaining the synthesis of intrathecal antibodies. Traditional B-cell depleting agents, such as rituximab may deplete short-lived plasma cells and plasmablasts derived from activated B cells but not CD20-negative long-lived plasma cells (14), which may contribute to treatment failure in severe NMDARE cases. Given these pathological insights, plasma cell-targeted therapy has emerged as a promising area of research (15). Daratumumab, an anti-CD38 monoclonal antibody, exerts its therapeutic effects by specifically eliminating short-lived and long-lived plasma cells and plasmablasts that express high levels of CD38. The drug has demonstrated high efficacy in multiple myeloma (16) and exhibits immunomodulatory functions on some other cells, including effector memory CD8^+^ T cells (17). Recent case reports indicate that daratumumab has significant potential for the treatment of refractory AE (18, 19). In parallel, the ongoing phase 2B EXTINGUISH trial is evaluating inebilizumab, an anti-CD19 antibody that depletes a broader spectrum of B-lineage cells including plasmablasts and some plasma cells, in a randomized, placebo-controlled design involving 116 patients with moderate-to-severe NMDAR encephalitis, with primary outcome assessed at 16 weeks (20). It remains to be determined whether early use of plasma cell depleting treatment provide more benefits in patients with severe AE. This trial aims to investigate the efficacy of daratumumab add-on ofatumumab in patients with severe AE and autoantibodies against neural surface antigens.

## Methods

2

### Trial design and setting

2.1

RADIA is a randomized, controlled, open-label, multicenter clinical trial initiated by investigators to assess the safety and efficacy of B-cell depleting therapy followed by daratumumab in patients with severe AE, with NMDARE as the primary target population. The study will be conducted in the Department of Neurology in 58 tertiary hospitals nationwide, with a planned enrollment of 200 patients by December 2026.

The study was approved firstly by the Institutional Review Board of the Third Affiliated Hospital of Soochow University. The first patient was randomized in Jan 2025. The participants will be randomly assigned to receive one of three treatment arms: B-cell-depleting agents (ofatumumab followed by daratumumab, B-cell-depleting agents (ofatumumab alone), or repeated IVIG/PE therapy. The flowchart outlining the recruitment, intervention, and evaluation processes is presented in Figure 1.

**Figure 1 fig1:**
[figure not shown]
Outline of the study procedure. OFA, ofatumumab; Dara, daratumumab; pts., patients; w, week; mRS, modified Rankin Scale; CASE, clinical assessment scale for autoimmune encephalitis; MMSE, mini-mental state examination; MoCA, Montreal cAssessment; NPI, neuropsychiatric inventory.

### Study population

2.2

#### Inclusion criteria

2.2.1

The patient inclusion criteria were as follows:Aged 12 years and older.Diagnosis of autoimmune encephalitis targeting neural surface antigen, predominantly NMDARE.At least 3 days of high-dose methylprednisolone pulse therapy (500–1000 mg) and IVIG (0.4 g/kg/day for 5 consecutive days), at least 5 sessions of plasma exchange or immunoadsorption, or at least 2 doses of FcRn antagonist efgartigimod have been used.mRS score ≥3 and neuropsychiatric manifestations inadequate to symptomatic treatment.Provision of informed consent by the participant or legal guardian.Negative pregnancy test for women of childbearing potential (up to 2 years postmenopause).

After providing informed consent, participants will enter a 14-day screening period. For individuals unable to provide consent owing to the severity of their condition, a legally authorized representative (or an equivalent individual as specified by local law) may provide informed consent, ensuring compliance with local regulations.

#### Exclusion criteria

2.2.2

The exclusion criterion was as follows:The investigator determined that the participant had a severe active or chronic infection.Participation in another clinical study involving investigational treatment within 4 weeks or 5 half-lives of any previously reported investigational therapy (whichever is longer) prior to randomization.Women who are pregnant, breastfeeding, or planning to become pregnant at any time within 6 months after the last dose of the study drug.A known history of allergies or reactions to any component of the study drug formulation or a history of allergic reactions following any biological therapy.Screening tests confirming positive serology for hepatitis B (HBsAg and/or anti-HBc positive) and/or positive PCR for hepatitis C.A history of cancer, except for ovarian teratomas (also known as dermoid cysts), germ cell tumours or nonmelanoma skin cancers (such as squamous cell carcinoma or basal cell carcinoma). Treatment for squamous cell carcinoma and basal cell carcinoma must have been successfully completed with documented cure at least 3 months prior to randomization.Administration of any live or attenuated vaccines within 3 weeks prior to enrollment (inactivated vaccines may be administered).Administration of the Bacillus Calmette–Guérin (BCG) vaccine within the past year prior to enrollment.

### Randomization and treatment allocation

2.3

Randomization is performed using a dedicated and password-protected clinical trial platform, Data Acquisition Platform–Electronic Data Capture system (DAP-EDC). Eligible patients are assigned in a 2:2:1 ratio to the three treatment groups. Stratified block randomization was applied, with study center as the stratum. Subjects were allocated sequentially according to their enrollment time.

### Informed consent procedure

2.4

Before participating in the clinical trial procedures, participant’s guardian will voluntarily complete and sign an informed consent form. The consent form will be paper-based, and a licensed physician will explain its contents, giving the participant sufficient time to make an informed decision. The consent of the research participants must be obtained in accordance with the ethical principles and standards outlined in the Declaration of Helsinki. All consent forms used will be those approved by the IRB, and a copy of the signed consent form will be provided to the participant. If the consent form is amended, the changes will be explained, and the consent process will be repeated.

For participants aged 12–18 years, written informed consent will be obtained from the participant’s legal representative, and written assent will also be obtained from the adolescent participant whenever appropriate, in accordance with institutional ethics requirements for pediatric research (21).

For participants who are unable to provide informed consent due to impaired consciousness or severe neuropsychiatric symptoms related to NMDARE, written informed consent will be obtained from a legally authorized representative (such as a parent, spouse, or other legally recognized representative) in accordance with institutional ethical requirements. Documentation verifying the legal relationship between the representative and the participant will be required. If the participant later regains decision-making capacity, the study procedures will be explained again and written informed consent will be obtained directly from the participant whenever possible.

### Study intervention

2.5

The RADIA trial includes a 14-day screening period used to determine participant eligibility. Prior to this screening period (specifically, within 90 days before randomization), individuals must have received first-line treatments such as high-dose intravenous corticosteroids, intravenous immunoglobulin (IVIg), and/or plasmapheresis. Importantly, participants who have received at least 2 doses of FcRn antagonist efgartigimod are still eligible for enrollment. The treatment period of the RADIA trial begins at the time of randomization. Participants will be randomized to receive either BCDT followed by daratumumab, BCDT, or repeated IVIG/PE.

The strategy of BCDT refers to multiple sclerosis. Anti-CD20 ofatumumab is administered subcutaneously at a dose of 20 mg at weeks 0, 1, and 2 (loading doses), followed by 20 mg every 4 weeks from week 4 to week 24 (maintenance doses: weeks 4, 8, 12, 16, 20, 24).

Daratumumab will be administered intravenously on the day after each ofatumumab administration. The daratumumab dosing schedule is: 8 mg/kg at weeks 0, 1, 2, and 4 (loading dose), followed by 4 mg/kg at weeks 8, 12, 16, 20, and 24 (maintenance dose). Pre-medication (corticosteroids, antihistamines, and antipyretics) is required before each daratumumab infusion to minimize infusion-related reactions.

In this study, each administration of daratumumab is defined as one treatment cycle. A total of 9 administrations are planned at weeks 0, 1, 2, 4, 8, 12, 16, 20, and 24, resulting in a total treatment duration of approximately 24 weeks. The effects of this daratumumab regimen will be evaluated throughout the study period. Laboratory tests will be required before each dose of the study drug to determine if any dose adjustments are necessary. During the study, patients should receive comprehensive supportive care as appropriate, aligned with their institutional guidelines. Necessary concomitant medications or treatments to ensure adequate supportive care, such as anti-epileptic drugs, may be prescribed. The following concomitant medications are strictly prohibited during the study: natalizumab, cyclosporine, mitoxantrone, mycophenolate mofetil, and azathioprine.

For adolescent patients aged 12–18 years, the doses of study drugs are consistent with the dosing regimen for adult patients. The safety and efficacy of ofatumumab in this age group have been established, and the dose is identical to that used in adults (22–25).

### Study measurements and data collection

2.6

Disease severity will be evaluated via mRS and CASE, See Table 1 for the specific schedule of assessments for each visit.

**Table 1 tab1:** Schedule of enrolment, interventions, and assessments.

	Study period																			
	Screen	Treatment phase													Follow-up					
Time point (week)	−1	0	1	2	3	4	5	6	7	8	12	16	20	24	28	32	36	40	44	48
Enrolment																				
Informed consent	**×**																			
Demographics	**×**																			
Medical history	**×**																			
Inclusion/exclusion	**×**																			
Intervention																				
Ofatumumab		**×**	**×**	**×**		**×**				**×**	**×**	**×**	**×**	**×**	Depends on the level of memory B cells monitored					
Daratumumab		**×**	**×**	**×**		**×**				**×**	**×**	**×**	**×**	**×**						
Rituximab		**×**												**×**	Depends on the level of memory B cells monitored					
IVIG/PE						**×**				**×**	**×**									
Assessments	×																			
HCG test (for female participants)	**×**																			
Physical examination	**×**	**×**	**×**	**×**	**×**	**×**	**×**	**×**	**×**	**×**	**×**	**×**	**×**	**×**	**×**	**×**	**×**	**×**	**×**	
Clinical blood tests and biochemistry	**×**		**×**	**×**		**×**				**×**	**×**	**×**	**×**	**×**			**×**			**×**
Cerebrospinal fluid (CSF) Analysis	**×**																			
Serum immunoglobulin and anti-NMDAR antibody levels	**×**					**×**				**×**	**×**	**×**	**×**	**×**			**×**			**×**
CSF anti-NMDAR antibody levels)	**×**																			
Lymphocyte Subsets	**×**		**×**	**×**		**×**				**×**	**×**	**×**	**×**	**×**			**×**			**×**
Memory B cells and plasma cell subsets	**×**		**×**	**×**		**×**				**×**	**×**	**×**	**×**	**×**			**×**			**×**
mRS	**×**	**×**	**×**	**×**	**×**	**×**	**×**	**×**	**×**	**×**	**×**	**×**	**×**	**×**	**×**	**×**	**×**	**×**	**×**	**×**
CASE	**×**	**×**	**×**	**×**	**×**	**×**	**×**	**×**	**×**	**×**	**×**	**×**	**×**	**×**	**×**	**×**	**×**	**×**	**×**	**×**
MMSE	**×**	**×**	**×**	**×**	**×**	**×**	**×**	**×**	**×**	**×**	**×**	**×**	**×**	**×**	**×**	**×**	**×**	**×**	**×**	**×**
MOCA	**×**	**×**	**×**	**×**	**×**	**×**	**×**	**×**	**×**	**×**	**×**	**×**	**×**	**×**	**×**	**×**	**×**	**×**	**×**	**×**
NPI	**×**	**×**	**×**	**×**	**×**	**×**	**×**	**×**	**×**	**×**	**×**	**×**	**×**	**×**	**×**	**×**	**×**	**×**	**×**	**×**
Imaging	**×**													**×**						**×**
Concomitant medications and dosage	**×**	**×**	**×**	**×**	**×**	**×**	**×**	**×**	**×**	**×**	**×**	**×**	**×**	**×**	**×**	**×**	**×**	**×**	**×**	**×**
Statistical analysis												**×**								**×**

Assessments will be conducted by the study team before randomization; after each study drug cycle at weeks 6, 16, and 24; and during follow-up at week 48. Neurocognitive performance will be measured via the Mini-Mental State Examination (MMSE), the Montreal Cognitive Assessment (MoCA), and the Neuropsychiatric Inventory (NPI) will be anti-neuronal antibody titres and other relevant markers will be analysed in serum and cerebrospinal fluid at baseline and week 16 following the initiation of the study drug treatment. For further details, please refer to the enrollment, intervention, and assessment schedule outlined in Table 1. Routine blood parameters will be assessed before each administration of the study drug, on day28 after each cycle, and at week 16 to monitor for potential drug-induced side effects, including thrombocytopenia, leukopenia, and elevated liver enzymes. Additionally, the length of stay in the ICU after the commencement of the study drug will be recorded at the conclusion of the study. Adverse events, including serious adverse events (SAEs), will be monitored continuously from the first administration of the study drug until 1 year after treatment initiation or until withdrawal from the clinical trial, whichever occurs first. Safety monitoring will therefore cover both the treatment period (up to Week 24) and the subsequent follow-up period (Weeks 24–48).

To reduce assessment bias, all outcome evaluations, including mRS, CASE, and neurocognitive assessments are performed by trained neurologists who are not involved in treatment allocation. All assessment sessions are video recorded and subsequently reviewed by at least one additional independent neurologist blinded to treatment group assignment. In cases of discrepancy, a third independent neurologist adjudicates the final score, ensuring that final outcome scores are based on a blinded adjudication process.

Patient safety monitoring: An independent Data Safety Monitoring Board (DSMB) will be established to oversee patient safety throughout the trial. The DSMB will review unblinded safety data at regular intervals, including cumulative serious adverse events (SAEs), adverse events of special interest (e.g., infusion-related reactions, infections, cytopenias), and protocol deviations. Meetings will be convened every 4 weeks during the treatment phase (weeks 0–24) and every 8 weeks during the follow-up phase (weeks 24–48), with *ad hoc* meetings as needed based on safety signals. Adverse events (AEs) and serious adverse events (SAEs) will be assessed and graded by site investigators using the Common Terminology Criteria for Adverse Events (CTCAE) version 5.0. All AEs and SAEs will be recorded in the electronic Case Report Forms (eCRFs) and reported to the DSMB within 24 h of identification. Causality assessments will be performed by the site investigators and independently reviewed by the DSMB. Safety data will be collected at every scheduled visit as outlined in Table 1. The DSMB will provide recommendations to the sponsor regarding trial continuation, modification, or termination based on pre-specified safety stopping criteria. Safety reporting will follow the CONSORT harms guidelines to ensure transparent and comprehensive documentation of all adverse events.

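### Table 1 schedules the pregnancy test at screening only, so no dosing visit has a test that would stop dosing in an unrecognised pregnancy

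*Protocol article*

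**What the plan says.** Section 2.2.1 makes entry conditional on "Negative pregnancy test for women of childbearing potential (up to 2 years postmenopause". Section 2.2.2 excludes women who are pregnant or breastfeeding, and those "planning to become pregnant at any time within 6 months after the last dose of the study drug".

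Section 2.5 states: "The RADIA trial includes a 14-day screening period used to determine participant eligibility". It then sets ofatumumab at weeks 0, 1, 2, 4, 8, 12, 16, 20 and 24. In the combination arm, daratumumab follows on the day after each ofatumumab dose.

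Section 2.6 directs the reader: "See Table 1 for the specific schedule of assessments for each visit". In that table the row "HCG test (for female participants" carries one mark, in the screening column. The follow-up columns of the ofatumumab row read "Depends on the level of memory B cells monitored". The row "Physical examination" is marked at every dosing visit. Section 2.6 also says: "Routine blood parameters will be assessed before each administration of the study drug".

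**The concern.** The eligibility criteria treat pregnancy as unacceptable at entry and for 6 months after the last dose. The visit schedule does not carry that standard through the 24 weeks of dosing in between. A site working from Table 1 would test once and then dose nine times without repeating the test. Screening can last 14 days, and no test at week 0 closes that gap.

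This is a patient-safety matter. It does not touch the endpoint, power or type I error. It concerns women of childbearing potential in the two ofatumumab arms, which together hold 80 + 80 = 160 of the 200 planned patients, both sexes counted.

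Clinical recognition may be slow here. Enrolment starts at age 12, and section 2.4 provides for patients with impaired consciousness or severe neuropsychiatric symptoms, who may not report a missed period.

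**Working it through.** **Reading the table.** The ofatumumab and daratumumab rows each have 9 marks, at the nine weeks given in section 2.5. Because these rows agree with the text, a column shift in the printed table is an unlikely explanation for the HCG row.

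| Row in Table 1 | Marks at the 9 dosing visits |
|---|---|
| HCG test | 0 |
| Physical examination | 9 |
| Clinical blood tests | 8 (week 0 blank) |

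On Table 1 time points the only test is at week −1, which is 24 − (−1) = 25 weeks before the last fixed dose.

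**Whether other text fills the gap.** Section 2.5 requires laboratory tests before each dose, for dose adjustment. Section 2.6 gives the purpose of the routine bloods as detecting drug side effects such as cytopenias and raised liver enzymes. Section 2.8 lists the individual termination criteria, and pregnancy is not among them. None of these places names a pregnancy test.

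**Counting exposed visits.** Let *c* be the week of conception, *r* the weeks until clinical recognition and *L* the weeks until a test is positive. The document gives neither *r* nor *L*. I assume *r* = 4 to 16 weeks or never, and *L* = 1.5, 2 or 3 weeks.

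- As printed: exposed visits = number of dosing weeks from *c* up to, but not including, *c* + *r*.
- With tests at weeks 0, 4, 8, 12, 16, 20 and 24: dosing stops at the earlier of *c* + *r* and the first test week at or after *c* + *L*. The test precedes the dose that day.

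*Conception at week 6, as printed:*

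| Recognised after | Stops at week | Doses given at weeks | Visits |
|---|---|---|---|
| 4 weeks | 10 | 8 | 1 |
| 6 weeks | 12 | 8 | 1 |
| 8 weeks | 14 | 8, 12 | 2 |
| 10 weeks | 16 | 8, 12 | 2 |
| 12 weeks | 18 | 8, 12, 16 | 3 |
| 16 weeks | 22 | 8, 12, 16, 20 | 4 |
| Not before week 24 | – | 8, 12, 16, 20, 24 | 5 |

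With the added tests, *L* = 1.5 or 2 makes the week 8 test positive (7.5 and 8 are both ≤ 8), giving 0 visits. *L* = 3 puts the first positive at week 12, after the week 8 dose, giving 1 visit.

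*Missed at screening.* Screening falls at week −1 or −2, so conception lies between −2 − 3 = −5 and −1.

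- Recognised at 8 weeks: dosing stops between weeks 3 and 7, so 3 visits (0, 1, 2) or 4 (plus week 4).
- At 12 weeks: stops between weeks 7 and 11, so 4 or 5 visits.
- At 16 weeks: stops between weeks 11 and 15, so 5 or 6 visits.
- With the added tests: 0 visits if the week 0 test is positive. If not, the week 4 test is, after doses at weeks 0, 1 and 2, giving 3. The range is 0 to 3.

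*Conception spread evenly over weeks 4 to 24, mean exposed visits as printed:*

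- Recognised at 4 weeks: always one dose, so 1.00.
- At 8 weeks: (16 × 2 + 4 × 1)/20 = 1.80.
- At 12 weeks: (12 × 3 + 4 × 2 + 4 × 1)/20 = 2.40.
- With the added tests: a dose is given only if the next 4-weekly visit falls within *L* weeks of conception, so the mean is *L*/4. That is 1.5/4 = 0.38 to 3/4 = 0.75 in all three cases.

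**The case against.** The strongest reply is that Table 1 is not a complete list, so a blank cell does not prove that a test is not done. The text adds to the table elsewhere: CSF antibodies are measured at week 16 though the CSF rows are marked only at screening; blood is required before each dose though week 0 is blank; and ECG stopping rules exist without an ECG row. The pre-dose laboratory tests are not itemised and could include HCG in a full protocol that is not shown. This is fair, and it is why the point is confined to the schedule as printed. But in those examples the text supplies the missing item, and for pregnancy testing no text does. Nor is this simply a detail dropped in condensing: the article prints the row and places the test at screening alone.

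Three further objections stand in part.

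- The recognition and test delays are assumptions, and no number of women of childbearing potential is given. No expected count of exposed pregnancies can therefore be derived. The ranges with and without the tests also meet in one case: missed at screening and recognised at 8 weeks (3 to 4 against 0 to 3).
- Ofatumumab after week 24 appears only in Table 1, since section 2.5 ends dosing at week 24.
- The proposal tests at 7 of the 9 dosing visits, not all 9. Weeks 1 and 2 are left out, being covered by tests at weeks 0 and 4.

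The entry test, the exclusion of planned pregnancy, examinations at each dosing visit and the physician's right to withdraw a patient all reduce the risk. None of them is a repeat test.

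**Conclusion.** The point holds. Table 1 schedules no pregnancy test at any of the nine dosing visits, and none before the later ofatumumab doses that it allows. A pregnancy beginning at week 6 would be exposed at 1 to 5 further dosing visits depending on when it is recognised, against 0 or 1 with the added tests. One missed at screening would be exposed at 3 to 6 visits if recognised 8 to 16 weeks after conception, against 0 to 3. If women or clinicians recognise pregnancy by about 4 weeks, the mean falls only from 1.00 visit to between 0.38 and 0.75.

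The results rest on the assumed test delay of 1.5 to 3 weeks and on reading Table 1 as the schedule sites follow. Confidence is medium, because the full protocol may already contain further tests. The change is worth making for safety; it does not affect the trial's statistical validity.

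**What to change.** In Table 1, for women of childbearing potential, mark HCG before dosing at weeks 0, 4, 8, 12, 16, 20 and 24, and before any later ofatumumab dose. Add a footnote: on a positive result, withhold study drug and keep the woman in safety follow-up. If the full protocol already requires these tests, correct Table 1 to show them.

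The cost is one table row, a footnote and an inexpensive assay. Table 1 already marks blood tests at weeks 4, 8, 12, 16, 20 and 24. It marks none at week 0 and, in follow-up, only at weeks 36 and 48. Week 0 and some later ofatumumab doses may therefore need a sample that the table does not show, although section 2.6 already calls for blood before each administration. Sample size and analysis are unchanged.
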